## Research design and methodology

This will be a prospective controlled before and after study involving two centres: the McGill University Health Centre (MUHC) Glen Site (Royal Victoria Hospital) and the Montreal General Hospital. The control and intervention units will be the five medical units.

The study will begin in the control period. Based on previous study data regarding the prevalence of admitted gabapentinoid users and the average number of monthly admissions on the clinical teaching units, recruitment in the control period should last approximately 12 months. All study sites will simultaneously transition to the intervention period after 80 patients have been recruited (estimated 1 year). The rationale for simultaneous transition of all units is to reduce the risk of inter-site contamination of the intervention, as it is common for medical residents and staff to work in all the study sites during a given year. The decision to transition to the intervention period after 80 patients have been recruited is motivated by the need to reduce the risk of bias introduced by temporal trends in deprescribing secondary to level of training of junior residents and seasonal variations of workload on the medical wards. If the target number of control participants is reached before the 12-month mark, recruitment will be suspended until then. The intervention period will be completed once the pre-specified target number of 80 intervention participants is reached, which is expected to take approximately 12 months as well.

Follow up of discharged patients will be at 8 weeks post-discharge. We will analyze and publish the results afterwards.

### Controls

All units will serve as their own controls during the initial control period. During this period, participants admitted to the medical ward with gabapentinoid use pre-admission (which are referred to as "gabapentinoid users") will receive usual medical care (pharmacy medication reconciliation). Although they will be informed that the goal of the trial is to evaluate medications and changes post discharge, they will be unaware that gabapentinoids are specifically targeted, so as to reduce the risk of contamination of the control arm. Furthermore, the medical staff will not receive specific information about the trial, or particular instructions with regards to deprescription during the control period.

### The intervention

The intervention will include the following components:

#### ***1. In-hospital patient educational brochure:***

Participant's medication list will be identified from the pharmacy database and validated with the participant's best possible medication history taken at time of admission by the pharmacist. Eligibility will be confirmed by the participant's treating medical team with support from the study investigators. Participants who are enrolled during the intervention phase will receive an educational brochure (see appendix) about the risks of chronic gabapentinoid use and how to stop using them. The rationale for the structure of the brochure has been presented in detail [24] and it has been validated in both English and French for comprehension and readability, including for people with mild cognitive impairment [27].

#### ***2. Educational session toward physicians about gabapentinoid prescriptions:***

An educational session about the purpose of the study and risks of gabapentinoid prescriptions will be delivered to physicians (staff and medical residents) on each unit at both sites during the intervention period. The educational session will include a presentation by a member of the team at the monthly teaching rounds and an electronic message sent to all physicians on the medical service. They will also be presented a brief overview of the educational brochures.

### Participant selection and recruitment

Any patient aged 60 years or older that has a prescription for gabapentin or pregabalin will be evaluated for the study by a research assistant. The 60 year cutoff was chosen based on retrospective data from the MUHC which identified that 75% of gabapentinoid users admitted to the medical CTU were aged 60 years and older. [8] Furthermore, given the increased prevalence of polypharmacy in older adults and its association with higher risks of adverse drug effects, this population would benefit most from

strategies to improve deprescription of potentially inappropriate medications. Patients will be screened with automated reports of active medications of inpatients provided by the institutional pharmacy. Pre-admission use of gabapentinoids will be confirmed with the medication history obtained by the unit's pharmacist at time of admission. If medication history is not available, then the admission note of the medical team will be used for confirmation. A research assistant will meet with members of the medical team to inform them of the eligibility of subjects for the study. A member of the medical team will then present the study to these potential participants and inquire if they would be interested in receiving further information. If so, they will subsequently be met by the research assistant.

## **Inclusion and exclusion criteria**

### *Inclusion criteria:*

- All inpatients 60 years or older admitted to study units who have a gabapentinoid prescription pre-admission. The 60-year cut-off was selected as it was felt this group would benefit the most from a deprescribing intervention, given the higher prevalence of polypharmacy and risk for potential adverse drug events. The deprescribing brochures are also designed with the input of older adults and specifically address changes in physiology that accompany the aging process to underscore the risks of gabapentinoids. Based on published retrospective data from the MUHC, approximately 75% of admitted gabapentinoid users are aged 60 and older [8].

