Distribution of educational brochures to hospitalized patients has been shown to be effective in improving successful deprescription of potentially inappropriate medications [9]. The brochures are standardized 8 to 10-page letter size documents, written in a sixth-grade level vocabulary for ease of comprehension. Examples are available on the Canadian Deprescribing Network website. Specific documents exist for different classes of potentially inappropriate medications, such as sedative-hypnotics, opioids, gabapentinoids and proton pump inhibitors. They contain self-assessment tests on risks of medications, provide information on evidence of efficacy and common side effects, propose therapeutic alternatives and suggest tapering regimens in the form of illustrated calendars. Patients are clearly informed to contact their healthcare providers prior to discontinuing or tapering their medication. Distribution of these educational brochures during hospitalization in chronic sedative users lead to a discontinuation rate of 64% at 30 days post-discharge, versus 21% with usual care [9].

In this trial, we aim to demonstrate that distribution of educational brochures during hospitalization to chronic gabapentinoid users can lead to improvement of successful deprescription. We hope that the brochures will inform patients of the limited evidence to support use of gabapentinoids and the risks of common side effects, motivating them to attempt discontinuation. As clearly stipulated in the brochures, the patients are expected to reach out to a healthcare provider to discontinue the drug, as gabapentinoids need to be gradually tapered to prevent rebound seizures, even in the absence of an underlying seizure disorder. These healthcare providers can either be staff or residents on the medical ward at the time of hospitalization, or a family physician in the community after discharge. By improving deprescription of gabapentinoids, we hope to reduce off-label use and, consequently, unnecessary exposure to potential undesirable side effects, leading ultimately to improved quality of life.

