## **Our primary objective is to facilitate the deprescription of gabapentinoids using a patient educational brochure.**

Specifically, we aim to:

1. **Primary outcome: evaluate the effectiveness of the patient empowerment intervention tool for deprescription of gabapentinoids in a hospital-based setting** as measured by the proportion of patient with a gabapentinoid prescription deprescribed (stopped or with an intent to taper to discontinuation) at 8-weeks post-hospital discharge.

This patient empowerment tool is a 10-page brochure based on social constructivist learning and self-efficacy theory. This will be paired with brief monthly orientation sessions for the medical staff and residents of the participating clinical teaching units during the intervention phase. These sessions will review the evidence for efficacy of gabapentinoids and introduce the use of educational pamphlets. Our primary endpoints will be sustained cessation of pre-hospital use at 8 weeks post-discharge. Discontinuation will be confirmed with consent to access to the *Dossier Santé Québec* (DSQ) and, as necessary to contact the respective community pharmacy of the participants.

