## **Justification of sample size**

The estimated sample size is 160 participants, with 80 in the control group and 80 in the intervention group. The sample size was calculated to detect an absolute increase of 20% in deprescription rates with the intervention (number needed to treat 5), allowing for a two-sided type 1 error of 5% and a type 2 error of 20%. Based on the results of a previous retrospective descriptive study of gabapentinoid prescriptions in medical inpatients, the control period event rate (discontinuation) is expected to be 13% [8]. The expected loss to follow-up is approximately 15%, including deaths.

There are approximately 50 patients admitted per month on each clinical teaching unit (total 200 admissions across the study units), of which 13% are expected to be taking gabapentinoids prior to admission [8]. Approximately 75% of admitted gabapentinoid users are aged 60 years and older. Assuming a refusal rate of 15%, as seen in the EMPOWER study [26], we expect a maximum of 16 participants enrolled per month.

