#### **2. Evaluate the effectiveness of a hospital-based deprescription intervention for unnecessary gabapentinoid prescriptions.**

Participants will be grouped by control and intervention based on the timing of the study. The primary outcome will be the complete cessation of gabapentinoid use or intent to taper to discontinuation (prescribed taper) measured at 8-weeks post hospital discharge. A secondary outcome will be measured as a dose reduction, without any intent to taper to discontinuation (decrease in medication use after

exposure to the intervention but no taper to complete cessation prescribed at the time of the 8-week study follow-up period).

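### A taper to discontinuation prescribed before admission does not bar entry and counts as a primary-outcome success at 8 weeks, so patients admitted mid-taper already satisfy the endpoint in either period

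*Protocol*

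**What the plan says.** **Entry.** Under Inclusion criteria the Protocol admits "All inpatients 60 years or older admitted to study units who have a gabapentinoid prescription pre-admission". The section on participant selection and recruitment adds that "Pre-admission use of gabapentinoids will be confirmed with the medication history obtained by the unit's pharmacist at time of admission", with the medical team's admission note as fallback. This check establishes use. It does not establish how long the drug has been taken or whether a taper is in progress. The Exclusion criteria cover age, seizure disorder, drug-plan and database enrolment, prognosis, consent, cognition, language, literacy and telephone contact. None concerns a taper or stop already prescribed.

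**Event.** The data analysis section (item 2) defines the primary outcome as "complete cessation of gabapentinoid use or intent to taper to discontinuation (prescribed taper) measured at 8-weeks post hospital discharge". The primary objective section gives the same two-part event and then adds "Our primary endpoints will be sustained cessation of pre-hospital use at 8 weeks post-discharge". Neither wording says that the cessation or taper must have started after admission or enrolment. By contrast, item 2 describes the secondary dose-reduction outcome as a decrease that follows the intervention.

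**Population wording.** The objectives section aims to show that "distribution of educational brochures during hospitalization to chronic gabapentinoid users can lead to improvement of successful deprescription", and the brochure is described as being "about the risks of chronic gabapentinoid use and how to stop using them". The Controls section defines users more broadly, as "participants admitted to the medical ward with gabapentinoid use pre-admission". The primary outcome statement likewise speaks of patients with a gabapentinoid prescription and does not require chronic use.

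**The concern.** The primary outcome should count deprescribing that the brochure and the physician sessions could have brought about. A taper prescribed in the community before admission cannot have been started by either. Where such patients are equally common in both periods, they add the same successes to each side and shrink the difference.

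Where they are not equally common, the difference itself is distorted. The periods run one after the other, and the treating team makes the first approach to patients. In the control period that team is not told the specifics of the study and participants do not know that gabapentinoids are the target; in the intervention period the team is briefed on gabapentinoid prescribing. A change in who is put forward or agrees is plausible, though nothing in the Protocol shows that it occurs. The planned adjustment is for age and sex only and would not in general remove such a shift.

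**Working it through.** **1. The plan's own figure.** Inputs from the sample size section: "the control period event rate (discontinuation) is expected to be 13"%, an absolute increase of 20 points, two-sided 5% error, 80% power and 15% loss.

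- Pooled-variance formula: n = [1.960 × √(2 × 0.23 × 0.77) + 0.842 × √(0.13 × 0.87 + 0.33 × 0.67)]² / 0.20² = 68.3, so 69 evaluable per group.
- Allowing for 15% loss: 69 / 0.85 = 81.2, so 82; or 69 × 1.15 = 79.4, so 80.

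The stated 80 per group is reproduced. The sample-size arithmetic is not in dispute.

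**2. Three patients traced through the text.**

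| Patient at admission | Eligible? | Counted at 8 weeks? |
|---|---|---|
| Community taper in progress, still prescribed at 8 weeks | Yes | Yes, as a prescribed taper |
| Community taper or planned stop, completed by 8 weeks | Yes | Yes, as complete cessation |
| Recent starter, no stop planned | Yes | Only if the drug is later stopped or tapered |

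In the first row the endpoint condition holds on the day of enrolment. In the second row the event was already set in train before admission. Screening on active inpatient medications removes patients already off the drug but neither of these. The third row is different: that patient is not an automatic success and can respond to the brochure.

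**3. Direction of the effect.** Let t be the share with a taper or planned stop prescribed before admission, s the probability that they are counted at 8 weeks (s = 1 if none is abandoned), p the control rate in everyone else and d the effect in everyone else. Take s as equal in both periods.

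- Control rate: (1 − t)p + ts
- Intervention rate: (1 − t)(p + d) + ts
- Difference: (1 − t)d

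With d = 20 points, each percentage point of t takes 0.2 point off the difference. By way of illustration only, t = 5% gives 19 points and t = 10% gives 18.

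If there is no true effect and the shares differ, the spurious difference is (t_intervention − t_control)(s − p). With s = 1 and p = 13%, each percentage point of imbalance produces 0.87 point; it can never produce more than 1. A shift from 5% to 10%, again assumed, would give 0.05 × 0.87 = 4.35 points. The sign follows the direction of the shift.

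**4. What is not known.** The Protocol gives neither t nor s, nor any change in t between periods. The value p = 13% is borrowed from the cited retrospective inpatient study, where it was measured at discharge in pre-admission users generally. It may already contain some mid-taper patients, and it omits stops between discharge and 8 weeks. Step 3 therefore shows direction and proportionality, not an estimate.

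**The case against.** The best case for the plan is that it is a pragmatic trial with broad entry, applied identically in both periods. With an equal mix, mid-taper patients only dilute the effect, which is conservative. Case-mix drift is a general risk of any before-after design, and nothing shows these patients to be more than rare. Medication-use history and prescription records are already collected, so they can be identified. All of this stands, and it limits the weight of the point. It does not repair the definition: no section says how a taper begun before admission is to be counted.

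A reader might infer more, in three ways that the Protocol does not support.

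- *That the trial fails to answer its own question because no minimum duration of use is set.* The primary outcome is stated for patients with a prescription, and the Controls section defines users by pre-admission use; both agree with the inclusion criterion. The word chronic stands in the narrative aim and in the description of the brochure. This is an inconsistency to reconcile. A minimum duration is a debatable choice in a pragmatic trial.
- *That short-course users in general cannot show an effect of the brochure.* A recent starter who would otherwise have continued can be deprescribed.
- *That a definite amount of power is lost.* This would need the share of such patients, which is not given, and would depend on how much of the 13% they already account for.

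**Conclusion.** The point holds in a narrow form. Entry does not exclude a taper or planned stop prescribed before admission, and the primary event has no start date, so a patient admitted mid-taper already satisfies the endpoint at enrolment and is counted unless the taper is abandoned. This dilutes the contrast in proportion to the share of such patients. It biases the contrast only if that share differs between the two non-randomised periods. The share is not in the Protocol; the effect may be small, and no figure for lost power or bias should be attached to it. The difference between chronic users and all pre-admission users is a secondary matter of consistency and does not show that the entry rule is wrong.

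**What to change.** 1. Add to the Exclusion criteria a taper to discontinuation or planned stop already prescribed before admission, verified in the admission medication history and the provincial prescription record.
2. In the primary objective section and in item 2 of the data analysis section, state that the event is a cessation or taper begun after admission, that is, during the index hospitalisation or later.
3. If control enrolment is complete, leave the intention-to-treat population as it is and apply the same pre-admission rule identically to both periods as a sensitivity analysis of the primary outcome. The rule uses only facts fixed before admission.
4. Reconcile the chronic-user wording in the objectives and brochure sections with the broader wording in the primary outcome, Controls and Inclusion criteria. Either apply the sponsor's own definition of chronic use at entry, or state the conclusion for all pre-admission users. Report duration of use by period from the prescription record.

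**Cost.** A few lines of text and a look-back in records that are already collected with consent. The eligible pool becomes slightly smaller. The Protocol expects at most 16 enrolments a month, against 80 / 12 = 6.7 needed. That maximum allows only for prevalence, age and refusal (200 × 0.13 × 0.75 × 0.85 = 16.6), so the real margin is narrower than the two figures suggest. The sensitivity analysis would rest on somewhat fewer patients.

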### *Exclusion criteria:*

- Less than 60 years of age
- Known seizure disorder
- Not being enrolled in the provincial drug plan (RAMQ)
- Opting out of the provincial drug database (*Dossier Santé Québec*), which will be confirmed by the patient at time of recruitment
- Previous enrollment in the study
- Patients expected to die before primary endpoint can be realized (e.g., patients admitted for end-of-life care or prognosis of 3 months or less)
- Unable to consent
- Major neurocognitive disorder, as determined by a previously established diagnosis or interim diagnosis by the medical staff on the ward of moderate severity or worse.
- Inability for patient to speak English or French
- Insufficient literacy in English or French
- No means of contacting patient by phone after discharge (for example, no valid phone number, traveling or planned discharge to facility without means of reaching by phone, etc.)

## **Justification of sample size**

The estimated sample size is 160 participants, with 80 in the control group and 80 in the intervention group. The sample size was calculated to detect an absolute increase of 20% in deprescription rates with the intervention (number needed to treat 5), allowing for a two-sided type 1 error of 5% and a type 2 error of 20%. Based on the results of a previous retrospective descriptive study of gabapentinoid prescriptions in medical inpatients, the control period event rate (discontinuation) is expected to be 13% [8]. The expected loss to follow-up is approximately 15%, including deaths.

There are approximately 50 patients admitted per month on each clinical teaching unit (total 200 admissions across the study units), of which 13% are expected to be taking gabapentinoids prior to admission [8]. Approximately 75% of admitted gabapentinoid users are aged 60 years and older. Assuming a refusal rate of 15%, as seen in the EMPOWER study [26], we expect a maximum of 16 participants enrolled per month.

## **Data collection**

Information about participants will be collected by the research assistants from the participants and their medical record. We will abstract reason for admission, comorbidities and other medications from the chart. At time of enrollment, we will obtain consent to directly obtain prescription history from the *Dossier Santé Québec* (DSQ), which is a prescription record database for all patients in Québec, as well as from the community pharmacy from which participants receive their medications. These will serve to validate deprescription. During the index admission, a first questionnaire will be administered in person and will collect information about demographics, including age, gender and residence style (independent, assisted living, etc.). We will also obtain a medication use history (for study drugs) and standardized questionnaires to assess global functioning, pain control and cognition. Follow up questionnaires will be administered at 8 weeks after hospital discharge by telephone. The follow-up questionnaire will collect any demographic changes such as destination of discharge and length of stay, will ask participants about deprescription (cessation, reduced use, intent to reduce, or no change), initiation or dose increase of other pain medications, occurrence of withdrawal symptoms, and finally will repeat the global functioning, pain control and cognition questionnaires.

Death will be determined from hospital records. Participants who are known to have died before 8 weeks post-discharge will be excluded from the analysis of the primary outcome (as they cannot attain it); however, they will be retained in the study for descriptive purposes and other outcomes.

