### *Blinding:*

It will not be possible to blind participants or physicians in this study. However, this is typical in pragmatic study designs, and we do not expect that this will have a substantial impact on our results. Blinding the assessment of outcome will be critical to ensure valid study results and we have tried to select as many hard outcomes as possible, including validated standardized questionnaires, that do not involve individual judgement by the assessor.

In the control period of this study, participants will be informed that the study will be evaluating medications and post-discharge changes but will not be aware that gabapentinoids will be specifically studied, in order to reduce selection bias. Accordingly, medical staff will not be aware of the specifics of the study during the control period.

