### **Ethical considerations, consent, privacy and confidentiality**

The study will be conducted in compliance with TCPS 2 (2018), as well as in respect of the requirements set out in the applicable standard operation procedures of the Research Institute of the McGill University Health Centre and of the McGill University Health Centre Research Ethics Board. Ethics approval will be obtained through the McGill University Health Centre Research Ethics Board.

Participant information will be compiled using the MUHC Research Institute REDCap software. Data will be coded with the use of a unique code for each participant. Access to the database will be limited to the study investigators and research assistants and will require a two-factor authentication. Only study investigators will have access to the final study data.

Some subjects may only agree to participate in the study if they are exempt from the follow up phone calls. Such patients will still be enrolled if they consent to our use of the DSQ to evaluate the primary endpoint but will be excluded from some of the secondary analyses.

Patients who are cognitively impaired or otherwise unable to provide consent will not be included. Although this subpopulation of patients may still greatly benefit from deprescription of potentially inappropriate medications, the educational brochures used in this study rely on instigating motivation and providing self-capacity, and are therefore intended for patients who are cognitively intact or have only a mild form of cognitive impairment [27]. Although distribution of the educational brochures to the patient's proxy could be considered, this strategy is less feasible in the context of the SARS-CoV-2 pandemic, as family and caregivers have limited access to the bedside, hindering contact with medical staff, which is crucial for initiation of the deprescription process.

Patients who are ultimately transferred to and discharged from non-study units during their hospitalization will be excluded unless that unit is a transitional care, rehabilitation, or post-acute care unit used only to bridge the gap between acute medical hospitalization and community services.

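### New analgesics and analgesic dose increases (secondary outcomes c and d) have only the participant's telephone report as a named source, although access to the prescription record is a condition of entry

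*Protocol*

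**What the plan says.** The Protocol's list of secondary outcomes includes starting new pain medications (c) and raising doses of current pain medications as a consequence of stopping the gabapentinoid (d), both at 8 weeks after discharge.

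The section Data collection says how they are obtained: "Follow up questionnaires will be administered at 8 weeks after hospital discharge by telephone". The call asks participants about deprescription and about "initiation or dose increase of other pain medications, occurrence of withdrawal symptoms". No other 8-week source is named for outcomes c and d.

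The same section describes a second data stream: "we will obtain consent to directly obtain prescription history from the *Dossier Santé Québec* (DSQ", "as well as from the community pharmacy from which participants receive their medications". The purpose given for these records is: "These will serve to validate deprescription".

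Access to the DSQ is a condition of entry, because the exclusion criteria list "Opting out of the provincial drug database (*Dossier Santé Québec*), which will be confirmed by the patient at time of recruitment".

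The sections Controls and Blinding say that participants cannot be blinded and that control-period participants are not told gabapentinoids are the drugs of interest. The section on ethical considerations allows enrolment of patients who decline the calls, with the primary endpoint taken from the DSQ, "but will be excluded from some of the secondary analyses".

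**The concern.** Starting a prescribed analgesic or raising its dose leaves a trace in a prescription record. The plan instead relies on what a person aged 60 or over, often on many drugs and recently in hospital, says by telephone. Intervention-period participants have received a brochure on gabapentinoid risks and alternatives, while control-period participants do not know which drug is under study. What is remembered and reported may therefore differ between periods for reasons unrelated to actual prescribing.

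The stake is the trial's view of substitution. The lay abstract and Background base part of the rationale on the danger of combining gabapentinoids with opioids. If stopping a gabapentinoid leads to more of other analgesics, opioids included, outcomes c and d are where this would appear. A reporting difference could hide such an effect or create one. Patients who declined the calls would not contribute at all.

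**Working it through.** **Is there a figure to reproduce?** The protocol gives none for outcomes c and d. Its 80 participants per period were derived for deprescription and do not bear on the choice of data source. The check is mainly a comparison of sections.

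**1. Source at week 8.** Data collection names the call for c and d. The records are tied to deprescription there, and the primary-outcome text likewise uses them to confirm discontinuation. The Statistical analysis plan section brings in the provincial record for patients who died or were lost, but only for gabapentinoid use. No section assigns a record to analgesic starts or dose increases.

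**2. Source at baseline.** Other medications are abstracted from the chart, and the medication history taken in person at enrolment covers the study drugs. For other analgesics, a chart list at baseline is thus followed by a participant's own account of change at week 8.

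**3. Availability of the record.** DSQ opt-outs are excluded and consent to DSQ access is taken at enrolment. The record should be available for essentially every participant.

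**4. Call-exempt patients.** They are enrolled, and their DSQ record is opened for the primary endpoint. With the call as the only named source, c and d would be missing for them. This follows from the source; the protocol does not say which secondary analyses they leave.

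**5. What unequal recall could do (illustration only).** The documents give neither an expected rate of new analgesics nor any recall accuracy, so all values here are assumptions. Let the true rate *t* be the same in both periods, let the call capture a share *s* of true starts, and assume no false reports. Then

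observed rate = *t* × *s*, and false difference = *t* × (*s* intervention − *s* control).

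| True rate | Capture 80% control, 80% intervention | 80%, 90% | 70%, 90% | 60%, 90% |
|---|---|---|---|---|
| 10% | 0 points | 1 | 2 | 3 |
| 20% | 0 points | 2 | 4 | 6 |
| 30% | 0 points | 3 | 6 | 9 |

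For example, at *t* = 20% with capture of 60% and 90%, the observed rates are 12% and 18%, a false difference of 6 points. Equal capture gives no false difference, only under-counting in both periods (20% × 0.8 = 16% observed). Exchanging the capture rates between periods reverses the sign.

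For scale, the 95% half-width for a difference between two rates of 20% with 80 per period is 1.96 × √(2 × 0.2 × 0.8 / 80) = 0.124, or 12.4 points. The false differences shown lie within sampling error for a single comparison, but unlike sampling error they would not average out.

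**The case against.** The strongest reply is that nothing forbids using the DSQ for these outcomes. The protocol says what the records will do without saying they will do nothing else, and precedence between sources is often settled in a later analysis plan or data manual. That is fair as far as it goes. But the protocol does fix a source for c and d, and it is the weaker of the two at hand. This is a choice already written down, beyond a detail left open.

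Second, call-exempt patients leave only some secondary analyses. Since every secondary outcome is in the telephone questionnaire, at least one must come from records. This stands, but dose reduction alone would satisfy it, so it does not show that c and d are record-based.

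Third, outcome d counts increases attributed to stopping the gabapentinoid, and no dispensing record shows why a dose rose. This stands fully: the telephone item has to be kept. The record also misses over-the-counter drugs and actual intake.

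Fourth, the DSQ consent of call-exempt patients is described for the primary endpoint. Wider use may exceed it, and the consent pages are not available to check. This too stands and shapes the fix.

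A reader might also infer more than the documents support:

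- *Gabapentinoid dose reduction has the same defect.* Data collection counts reduced use among the deprescription answers, and the records validate deprescription, so that outcome is arguably covered already.
- *The planned 15% loss, 12 of 80 per period, measures the missing telephone data.* That figure includes deaths, was set in the sample-size calculation for deprescription and is not a telephone non-response rate. Patients with no means of telephone contact are excluded at entry.
- *The Blinding section contradicts this choice by claiming "we have tried to select as many hard outcomes as possible, including validated standardized questionnaires".* That sentence concerns judgement by the assessor, and the standardized questionnaires are those for function, pain and cognition. It does not govern how the medication items are ascertained.

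**Conclusion.** The point holds for outcomes c and d. Their only named 8-week source is an unblinded participant's telephone report, awareness of the study target differs by period, and a record common to both periods is already accessible. The outcomes are therefore exposed to recall and reporting bias that could largely be avoided for prescribed drugs, and call-exempt patients would be lost from them unnecessarily.

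It would go too far to say that these outcomes are biased. The documents give no recall accuracy, the direction could be either way, and equal recall in both periods would produce no false difference. The range of 0 to 9 points rests wholly on the assumed true rates of 10% to 30%, capture of 60% to 80% in control against 80% to 90% in intervention, and no false reports. The number of call-exempt patients is not stated, so the number of participants recovered by using the record cannot be given.

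The primary outcome is unaffected. This is a correction to two secondary outcomes that should be made because it is cheap and because they are the trial's direct measures of substitution.

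**What to change.** In Data collection:

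1. Name the DSQ/community pharmacy record as the main source for prescribed analgesic starts and dose increases in all participants, including call-exempt ones.
2. Define both outcomes by comparing the pre-admission regimen with the regimen active at week 8, and report opioids separately.
3. Keep the telephone item as a supplement for non-prescription analgesics, actual intake and, for outcome d, whether an increase was attributed to stopping the gabapentinoid. Report all dose increases found in the record alongside the attributed ones, so that outcome d is not silently redefined.
4. Make sure that the DSQ consent wording for call-exempt patients, now described for the primary endpoint, covers this use.

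The cost is additional abstraction from a record that the study already opens for each participant, and possibly a change to the consent wording. The remaining weakness is that dispensing does not prove intake, which is one reason to keep the telephone item.
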